
##### Clinician/researcher-rated measures

Functioning will be assessed on the Global Assessment of Functioning (GAF) measure [16, 35]. GAF scores range from 1 (in some danger of hurting self or others) to 100 (absent or minimal symptoms), examining both symptoms and functioning. It has demonstrated good internal consistency (Cronbach’s *α* = .80).The Threshold Assessment Grid (TAG) examines the severity of participants’ mental health difficulties [43]. It has seven domains measuring three areas of safety, risk and needs and disabilities. Participants can score from 0 (none) to 4 (very severe) on each domain, which is analysed individually/as a total score. It has good internal consistency (Cronbach’s *α* = .70).

Participants’ clinical records will be examined to gather information on:Hospitalisation: Total number of days in hospital and number of incidentsRelapse: Total days under the care of acute mental health services (including inpatient wards, crisis home treatment, psychiatric liaison and acute crisis and assessment teams) and number of incidentsNumber of serious incidents and adverse events, including those of harm to self and others

### Qualitative interviews

Qualitative interviews will be conducted to explore service users’ and therapists’ experience of the crisis-focused CBTp intervention and research trial more broadly. This is to evaluate the acceptability of the therapy and therapists’ training.

Participants in the CBTp arm will be invited to complete a qualitative semi-structured interview exploring their experiences of the intervention and its perceived impacts. A purposive sampling approach will be undertaken to ensure a representative sample of participants. We will make efforts to ensure we recruit an ethnically diverse sample and include those who dropped out from therapy. The interview guide will include questions focusing on acceptability following guidance from Sekhon et al. [40] on examining acceptability including how they felt about the intervention, levels of burden, intervention coherence, perceived effectiveness and how it fitted with their value system. The interviews will be undertaken approximately 4 to 8 weeks post-intervention. We aim to interview half of the participants in the CBTp arm; therefore, an estimated total of *n* = 12–15 participants, depending on the quality, depth and diversity of data collected, as this is recommended as an adequate sample size for qualitative interviews analysed by thematic analysis [9]. A purposive sampling approach will be undertaken to ensure a representative sample of participants. 

Semi-structured interviews will also be conducted with the therapists delivering the CBTp intervention and examine perceived acceptability again following guidance from Sekhon et al. [40]. The sample size will be dependent on the number of therapists recruited to deliver therapy but it is estimated that this will be approximately four to six participants. The interview topic guide will include questions on the therapists’ impressions on the usefulness of the training, positive and negative aspects of the training and areas for development. The interview guide includes questions on therapists’ impressions of the usefulness of therapy, expectations and goals, positive and negative aspects of CBTp and relationship with the service user, and suggestions for treatment refinement. This is to evaluate the feasibility and acceptability of the training. The interviews will be undertaken once the therapist has completed all of their allocated therapy cases.

### Analysis plan

The study will follow best practice guidance for the reporting of feasibility RCTs (CONSORT, [13, 39]). The focus of the analysis will be on key indicators of feasibility, including participant recruitment, retention and acceptability of the intervention, which will be summarised descriptively using frequencies and percentages. Continuous clinical outcome measures will be summarised separately by study arm using means and standard deviations or medians and interquartile ranges, as appropriate for the distribution of the data. Binary outcome measures will be summarised using frequencies and percentages. The quantity of missing data for each clinical outcome will be examined and likewise summarised by study arm. This pilot study will not have sufficient power to assess the effectiveness of the intervention. However, to trial the analysis envisaged for a future, fully powered, effectiveness RCT, clinical outcomes at follow-up time points will be compared between study arms, using linear or logistic regression models as appropriate, and adjusting for the baseline measure of the outcome in question.

The qualitative interviews will be audio recorded, transcribed verbatim and analysed using thematic analysis [9] by LW on NViVo [33]. The thematic analysis will be conducted from a critical realist position and will combine inductive and deductive approaches, seeking both to explore participants’ experiences of receiving or delivering CBTp and to answer questions about the acceptability and feasibility of the therapy, its components and its mode of delivery. Initially, each transcript will be read and reread to ensure the researcher is fully immersed in the data, and then initially coded. Codes will be collated together across interviews and grouped together to form analytical themes. Patterns of themes will be explored across the data set focussing on both commonalities and variations and comparing service user and therapist perspectives. The theme structure will be checked with a small number of participants to check it reflects their experiences. The final theme structure will also be discussed with the research team and stakeholder group (including people with lived experience of psychosis and inpatient admission).

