## Methodology

### Design

This study will adopt a single-centre, individually randomised, parallel-group, RCT design with an embedded qualitative component. Participants will be randomly allocated to either treatment as usual (TAU) or CBTp plus TAU in a 1:1 ratio, as undertaken in other psychological therapy trials conducted in inpatient settings [20, 36]. Outcome measure assessments will be carried out at baseline, 2 months post-randomisation and 6 months post-randomisation either face to face or remotely. Relapse, rehospitalisation and adverse event data will be again examined 12 months post-randomisation. This protocol is reported following guidance from the SPIRIT tool (Standard Protocol Items: Recommendations for Intervention Trials, [10]). The trial has been registered on the ISRCTN trial registry (ISRCTN59055607). The study plan is outlined in Fig. 1 and the schedule of participant activities is in Table 1. Full Health Research Authority (HRA) and NHS Research Ethics Committee (REC) approval has been granted (IRAS ID: 272043; 20/LO/0137/AM01) and the study is sponsored by the University College London.

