### Sample size

We will aim to recruit sixty participants in line with recommendations by Consolidated Standards of Reporting Trials (CONSORT) for feasibility and pilot RCTs [13], thirty of which will be randomly allocated to the therapy arm and thirty to the TAU arm. A sample of sixty is deemed of sufficient size to examine the aims of the study. Data (relevant means and standard deviations) from this study will be used to inform a power calculation for a future larger multi-site trial. The sample size will also allow for dropouts, which are common in clinical trials in acute mental health inpatient settings. Some studies report attrition rates of over 50% [36], and recruiting a larger sample will still allow us to collect adequate data to inform a larger multi-site trial.

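### The regression rehearsed for the main trial makes no stated use of the 2-month scores at 6 months; a joint model of both visits would be a cheap, optional improvement

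*Protocol article*

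**What the plan says.** The Design section sets the visits: "Outcome measure assessments will be carried out at baseline, 2 months post-randomisation and 6 months post-randomisation". Under Sample size, sixty people are to be recruited, "thirty of which will be randomly allocated to the therapy arm and thirty to the TAU arm".

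The Analysis plan puts the weight on descriptive feasibility indicators and says plainly that "This pilot study will not have sufficient power to assess the effectiveness of the intervention". It then adds a comparison of arms, in these terms: "clinical outcomes at follow-up time points will be compared between study arms, using linear or logistic regression models as appropriate". No covariate is named beyond the one that follows from "adjusting for the baseline measure of the outcome in question". The purpose given for this comparison is "to trial the analysis envisaged for a future, fully powered, effectiveness RCT". On missing values the plan says only that "The quantity of missing data for each clinical outcome will be examined and likewise summarised by study arm". It names neither a repeated-measures model nor imputation.

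On expected loss, the Feasibility criteria ask for 75% retention at 2 months and 60% at a second time that is also printed as 2 months. The Sample size section notes that "Some studies report attrition rates of over 50" per cent.

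**The concern.** Ordinary linear or logistic regression takes one outcome value per participant. With contact visits at 2 and 6 months, the natural reading is one model per visit. The 6-month model then includes only those seen at 6 months, and it knows nothing of how people were doing at 2 months. Someone assessed at 2 months and lost afterwards adds nothing to the 6-month comparison.

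This matters if loss after 2 months depends on the 2-month state, and does so differently in the two arms. That is conceivable here, because only one arm has therapy contact that continues after discharge. The 6-month contrast would then be biased although the scores needed to correct it under missing at random have been collected. Because the comparison is a rehearsal, the consequence lies mainly in the later trial.

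**Working it through.** The article gives no power or effect-size calculation for n = 60, so there is no stated figure to reproduce on this point.

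**Step 1. Participants affected.** Inputs: n = 60 (Sample size); 75% and 60% (Feasibility criteria, the second read as 6 months, which is an assumption). Dropout is taken as monotone.
- Seen at 2 months: 60 × 0.75 = 45.
- Seen at 6 months: 60 × 0.60 = 36.
- Seen at 2 but not at 6 months: 45 − 36 = 9, which is 9/60 = 15% of those randomised and 9/45 = 20% of those seen at 2 months.

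**Step 2. Where bias would come from.** Write the 2-month score as Y2 = a0 + a1·arm + a2·baseline + error, and the 6-month score as Y6 = c0 + c1·arm + c2·baseline + c3·Y2 + error. The 6-month arm effect given baseline is c1 + c3·a1. A regression on those still present estimates c1 + c3·(a1 + δ), where δ is the extra arm difference in Y2, given baseline, created by who stays. So bias = c3·δ. If selection on Y2 works alike in both arms, δ is close to zero and so is the bias. If it differs by arm, the bias is c3·δ at any sample size.

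The documents give no correlations. Assume 0.5 for baseline to 2 months, 0.4 for baseline to 6 months, and r = 0.5 or 0.7 between 2 and 6 months. Then c3 = (r − 0.5 × 0.4)/(1 − 0.5²):
- r = 0.5: 0.3/0.75 = 0.40.
- r = 0.7: 0.5/0.75 = 0.67.

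**Step 3. Size.** Simulation: 6,000 replicates per scenario, N = 60, 75% seen at 2 months at random, about 60% at 6 months. The true effect is 0 or 0.4 SD. Where dropout depends on the 2-month score, its log-odds change by 1 per SD. All of these settings are assumptions. Bias of the 6-month regression on arm and baseline, in SD:

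| Dropout after 2 months | r = 0.5, effect 0 | r = 0.5, effect 0.4 | r = 0.7, effect 0 | r = 0.7, effect 0.4 |
|---|---|---|---|---|
| Random | 0.006 | 0.002 | 0.001 | 0.001 |
| Related to 2-month score, same in both arms | 0.001 | 0.008 | 0.005 | 0.018 |
| Related in TAU arm only | 0.054 | 0.053 | 0.092 | 0.096 |
| Related in therapy arm only | −0.049 | −0.047 | −0.096 | −0.078 |
| Opposite directions in the two arms | 0.110 | 0.119 | 0.173 | 0.206 |

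The likelihood estimate c1 + c3·a1, with a1 fitted on everyone seen at 2 months, had absolute bias of at most 0.006 SD in every cell. Its variance relative to the per-visit regression was 0.97 to 1.02 at r = 0.5 and 0.91 to 0.98 at r = 0.7. The sampling SD of the per-visit estimate was 0.30 to 0.32, so Monte Carlo error is about 0.31/√6000 = 0.004.

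**Step 4. Pilot against main trial.** In the pilot the bias is at most 0.21/0.31 = 0.68 of one sampling SD. For an assumed main trial of 400 with the same retention, the sampling SD is about 0.31 × √(60/400) = 0.12. A bias of 0.05 to 0.21 SD is then 0.05/0.12 = 0.4 to 0.21/0.12 = 1.75 standard errors.

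**The case against.** The strongest reply is that the article never says separate models, complete cases or discarding. It is silent on how missing values are handled, which is commonly left to an SAP, and imputation using the 2-month score followed by exactly the stated regression would keep these participants. That stands: the per-visit, unimputed reading is natural but inferred. What the article does fix is the model family, the single covariate and the rehearsal purpose, and those can be improved as stated.

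Four further points stand in whole or in part.
- A reader might infer that the 6-month comparison is biased. The documents do not support that. They give no dropout mechanism and no correlations, and two of the five mechanisms examined leave almost no bias. The largest values need dropout to run in opposite directions in the two arms.
- The joint model's near-zero bias is built into those scenarios, because loss there depends only on observed scores. When loss depended on the unobserved 6-month state, the joint analysis was still biased by about 0.10 to 0.14 SD (one arm) or 0.19 to 0.28 SD (opposite directions), against about 0.15 to 0.17 and 0.29 to 0.32 SD for the per-visit regression. That is an improvement, not a cure.
- A reader might call the planned regression markedly less precise. It is not; in some scenarios the joint model gains nothing.
- No feasibility criterion uses this contrast, and trialling an analysis does not bind the main trial. The retention figures are criteria, not forecasts.

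None of this removes the case for rehearsing the more robust analysis when that rehearsal is the comparison's stated purpose.

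**Conclusion.** The point holds as an optional, cheap improvement to the rehearsed analysis, not as an error in the pilot. On its natural reading the plan leaves the 2-month scores of about 9 of 60 participants unused at 6 months. The resulting bias ranges from negligible (at most 0.02 SD) to about 0.21 SD, depending on whether dropout relates to the 2-month score differently by arm. The case rests on robustness to such dropout in a larger trial, where sampling error shrinks and this bias does not, rather than on precision.

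The assumptions are the correlations, the dropout slopes, monotone loss, no imputation, and 60% being the 6-month criterion. Relapse, rehospitalisation and adverse events come from clinical records and are largely unaffected. The feasibility conclusions do not depend on this comparison.

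**What to change.** For continuous participant-assessed outcomes, name as the rehearsed analysis one linear mixed model for the 2- and 6-month values. Fixed effects: arm, time, arm-by-time, baseline and baseline-by-time. Use unstructured covariance and include everyone with at least one follow-up. An equivalent route is the stated regression after imputation from a model that includes the 2-month score. Report the arm contrast with a 95% CI at each time, and keep the single-time-point regression as a sensitivity analysis.

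The cost is a few lines of wording and code, with no new data. The model is slightly more complex and may need a fallback if it does not converge. It removes the bias only under missing at random, which the report should say. The second retention criterion, now also printed as 2 months, should be corrected at the same time.

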#### Feasibility criteria

The trial of the CBTp intervention will be deemed feasible if the following criteria, determined by examining published CBTp trials, are met [19, 49]:Retention rate of 75% at 2 months post-randomisation and 60% at 2 months post-randomisationRecruitment of ≥80% of the target sample size (*n* = 60) over the 12-month recruitment periodQualitative data from service users and therapists support the intervention/indicate that the intervention is acceptable.

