#### Crisis-focused CBTp intervention

The trial intervention will be delivered by psychological therapists working in the acute inpatient services. All therapists are clinical psychologists or counselling psychologists registered with the UK Health and Care Professions Council [HCPC], with experience of delivering CBTp in inpatient settings.

The crisis-focused CBTp intervention is underpinned by a modularised CBTp protocol that aims to deliver approximately six to eight sessions of therapy to participants. The protocol includes seven modules; engagement, assessment and identifying priorities; formulation of the crisis; stabilisation and safety; coping, self-management and problem solving; crisis plans and crisis cards; change strategy work focusing on crisis appraisals and safety behaviours; and discharge, relapse planning and recovery toolkits. The first two modules (engagement, assessment and identifying priorities, and formulating the crisis) are essential components of the intervention and the remaining ones are collaboratively chosen based on the participant’s priorities. The number of sessions will be determined by the collaborative priorities set by the service user and therapist and the length of admission, and therefore, more or less sessions can be offered. The therapy will also include at least one follow-up session post-discharge to ensure support through the discharge process. The intervention will also include strategies to involve the individual’s network, e.g. family sessions, and formulation sharing with the multi-disciplinary team.

The sessions will be delivered in a private and quiet room on the inpatient ward or outside/off the ward if the participant has the appropriate leave, e.g. in a room off the ward but on the grounds of the hospital. If the participant is discharged before therapy is complete, the sessions will continue and be delivered in community settings or remotely (e.g. via phone or video conferencing technology). This is to ensure that there is continuity in sessions post-discharge.

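### The retention criteria name no arm and cap no between-arm gap, so heavy loss in one arm can be offset by the other and still count as feasible

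*Protocol article*

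**What the plan says.** The Feasibility criteria section gives the only decision rule in the document: "The trial of the CBTp intervention will be deemed feasible if the following criteria" are met. There are three: retention (75% and 60%), recruitment of at least 80% of the target of 60, and qualitative data supporting acceptability. The retention criterion does not say whether it is judged overall or by arm, and it sets no limit on a difference between arms. Both percentages are printed against 2 months, although the Design section states "Outcome measure assessments will be carried out at baseline, 2 months post-randomisation and 6 months post-randomisation".

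The Sample size section plans 60 participants, "thirty of which will be randomly allocated to the therapy arm and thirty to the TAU arm", and notes of comparable inpatient trials: "Some studies report attrition rates of over 50" per cent.

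The Analysis plan lists the feasibility indicators, "including participant recruitment, retention and acceptability of the intervention, which will be summarised descriptively using frequencies and percentages", and again names no arm. It then says of the clinical outcomes: "The quantity of missing data for each clinical outcome will be examined and likewise summarised by study arm". No sentence connects that by-arm summary to the feasibility criteria.

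**The concern.** The verdict helps decide whether a full-scale trial may be warranted, and the analysis envisaged for that trial is a comparison of follow-up outcomes between arms. For that comparison, how evenly the arms are retained matters as well as how many are retained in total. A total can be reached by one arm making up for the other.

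Unequal retention is foreseeable from the design. In the therapy arm, "If the participant is discharged before therapy is complete, the sessions will continue and be delivered in community settings or remotely", with at least one follow-up session after discharge. Participants are told their allocation. For TAU participants the article describes no further trial contact between allocation and the 2-month assessment. The qualitative criterion offers little protection on the TAU side, because the participant interviews described are with the CBTp arm only.

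At stake is a feasible verdict resting on a retention pattern that would threaten the main trial's comparison, with no prompt to repair it first.

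**Working it through.** **Inputs.** From the protocol: 60 participants, 30 per arm (Sample size); allocation to "either treatment as usual (TAU) or CBTp plus TAU in a 1:1 ratio" (Design); thresholds of 75% and 60%, and a recruitment minimum of 80% (Feasibility criteria). Assumed here: retention means the proportion of those randomised who complete the assessment; the thresholds apply to the whole trial; true retention rates are illustrative. The protocol gives no calculation behind its thresholds, so there is no figure of its own to reproduce.

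**Step 1: what the overall thresholds allow.** Number needed K = threshold × N, rounded up. Lowest possible rate in one arm = (K − n)/n, where n is the arm size and the other arm is fully retained.

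| N (per arm) | Threshold | K | Lowest rate in one arm |
|---|---|---|---|
| 60 (30) | 75% | 45 | (45 − 30)/30 = 50% |
| 60 (30) | 60% | 36 | (36 − 30)/30 = 20% |
| 48 (24) | 75% | 36 | (36 − 24)/24 = 50% |
| 48 (24) | 60% | 29 | (29 − 24)/24 = 21% |

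The rows for 48 are the smallest recruitment that meets its own criterion (0.80 × 60 = 48), assuming an equal split.

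**Step 2: less extreme splits that pass with 30 per arm.**

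- 75% threshold: 28 + 17 = 45 (93% v 57%, a 37-point gap; Fisher exact p = 0.002).
- 75% threshold: 27 + 18 = 45 (90% v 60%; p = 0.015).
- 75% threshold: 26 + 19 = 45 (87% v 63%; p = 0.07).
- 60% threshold: 27 + 9 = 36 (90% v 30%).

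**Step 3: chance of passing.** With X and Y the numbers retained in two arms of 30, independent binomial with true rates p₁ and p₂, and f the minimum count required in each arm:

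P(pass) = Σ P(X = i) P(Y = j) over all i + j ≥ K with i ≥ f and j ≥ f.

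At the 75% threshold, K = 45. A 60% floor means f = 18; the strict rule of 75% in each arm means f = 23.

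| True rates | Overall only | With 60% floor | Strict per-arm |
|---|---|---|---|
| 75% / 75% | 57% | 57% | 26% |
| 80% / 80% | 87% | 87% | 58% |
| 90% / 60% | 57% | 49% | 4% |
| 95% / 55% | 57% | 35% | 1% |

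At the 60% threshold, K = 36. Floors of 45%, 50% and 60% mean f = 14, 15 and 18; the last is the strict per-arm rule.

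| True rates | Overall only | 45% floor | 50% floor | 60% floor |
|---|---|---|---|---|
| 60% / 60% | 55.6% | 55.3% | 54.4% | 33.5% |
| 80% / 40% | 56% | 27% | 17% | 2% |
| 90% / 30% | 57% | 4% | 2% | 0.1% |

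The overall rule passes a 90%/60% trial as often as a balanced 75%/75% one. The floors leave balanced trials almost untouched and reduce passing most when the gap is large.

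**The case against.** The strongest reply is that the trial-wide reading comes from silence. The criteria never say overall or pooled, and this is a condensed article whose full protocol may define the unit. That stands in part: trial-wide is the natural reading, not a stated one. But the article does print its feasibility rule, and nothing in that rule looks at retention by arm.

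Second, the imbalance would not be hidden. Missing data are summarised by arm, a steering committee with statistical expertise oversees the trial, and a pass only suggests that a larger trial may be warranted. This also stands. A reader might infer that differential loss would go unnoticed, and the documents do not support that. What remains is that it would be seen without counting in the verdict.

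Third, a reader might infer that a main trial with this pattern would be biased. That is too strong. Bias depends on why data are missing and on the analysis. Hospitalisation and relapse come from clinical records and need not be lost with the interview. No arm-specific attrition is given, so the splits above are hypothetical.

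Fourth, rates on 30 people are imprecise. This is decisive against a strict per-arm rule, which would cut a balanced 75%/75% trial's chance of passing from 57% to 26%. It does not count against the lower floors.

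**Conclusion.** The point holds as a weakness in how the decision rule is set, not as an error of calculation. On the trial-wide reading, the 75% threshold can be met with one arm as low as 50%, and the 60% threshold with one arm as low as 20%. A 28/30 v 17/30 split passes. The consequence is a risk of bias in the main trial's comparison that the rule cannot register.

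This rests on 30 per arm, on retention being counted among those randomised, and on the criteria not being defined by arm in a fuller document. The pass probabilities also depend on the assumed true rates. The 2-month label on both thresholds is a separate inconsistency in the same criterion. The second threshold probably belongs to the 6-month assessment, but the text does not say so.

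**What to change.** Keep the overall thresholds and add one sentence to the Feasibility criteria section: at the assessment with the 75% threshold neither arm may fall below 60%, and at the assessment with the 60% threshold neither arm may fall below a lower floor, for example 45–50%. A 60% floor there would simply be the strict per-arm rule. If only the overall threshold is met, the verdict becomes feasible with changes to retention procedures in the failing arm. State that retention is otherwise judged overall, and reconcile the time point printed for the second threshold with the assessment schedule in the Design section. The sentence should be fixed before retention by arm is examined.

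The cost is small. By-arm missing-data summaries are already planned, and with 30 per arm a balanced trial's chance of passing falls by about 1 percentage point at most (55.6% to 54.4% with the 50% floor at true 60%; no visible change at the 75% threshold). The limitation is that a floor stops severe one-arm loss only. Splits of 26/30 v 19/30 and 27/30 v 18/30 would still pass. If moderate gaps matter to the team, a stated maximum between-arm difference is the alternative, with the same imprecision at this sample size.

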**Discussion:**

Findings of this pilot RCT will indicate whether a larger multi-site RCT is needed to investigate the efficacy of the intervention. If the initial results demonstrate that this trial is feasible and the intervention is acceptable, it will provide evidence that a full-scale effectiveness trial may be warranted.

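### The feasibility verdict sets retention percentages against single cut-offs with no stated allowance for sampling error, although 48 to 60 participants fix these rates only to about ±11 to 13 points

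*Protocol article*

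**What the plan says.** The Sample size section sets the target: "We will aim to recruit sixty participants in line with recommendations by Consolidated Standards of Reporting Trials (CONSORT) for feasibility and pilot RCTs", 30 per arm. It justifies this by guidance and by allowance for dropout, noting that "Some studies report attrition rates of over 50" per cent. It does not link 60 to the precision of any feasibility rate.

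The Analysis plan makes recruitment, retention and acceptability the focus of the analysis, "which will be summarised descriptively using frequencies and percentages". The article mentions no interval.

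The Feasibility criteria section then states the decision rule. The trial "will be deemed feasible if the following criteria" hold:
- retention of 75% and of 60%, both printed as 2 months after randomisation;
- recruitment of at least 80% of 60 over 12 months;
- qualitative data from service users and therapists that support acceptability.

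Each numerical criterion has one cut-off. The Design section gives the assessment times: "Outcome measure assessments will be carried out at baseline, 2 months post-randomisation and 6 months post-randomisation". On the consequence, the Discussion paragraph of the Abstract says that if the trial proves feasible and the intervention acceptable, "it will provide evidence that a full-scale effectiveness trial may be warranted".

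**The concern.** The feasibility proportions are the pilot's main quantitative results, and retention is turned into a yes/no verdict as if it were measured without error. Retention somewhat below target can pass, and retention somewhat above target can fail, with appreciable probability. All the criteria appear to be required, so a narrow numerical miss gives a negative verdict whatever the interviews show. The verdict feeds the case for a full-scale trial. Given the attrition the protocol itself cites, observed retention near the cut-offs is plausible, and that is where a bare percentage misleads most.

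**Working it through.** **Inputs.** Target 60 (Sample size). Smallest acceptable recruitment 0.80 × 60 = 48 (Feasibility criteria). Retention cut-offs 75% and 60% (Feasibility criteria). The protocol gives no precision calculation to reproduce.

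**Assumptions.** The denominator is all participants randomised, and participants are independent. For joint figures, the 60% criterion refers to 6 months, and those retained at 6 months are a subset of those retained at 2 months.

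**Precision at the cut-off.** 95% Wilson interval: centre (p + z²/2n)/(1 + z²/n), half-width z√[p(1−p)/n + z²/4n²]/(1 + z²/n), z = 1.96.

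| Observed | Rate | 95% interval | Half-width (points) |
|---|---|---|---|
| 45/60 | 75% | 62.8 to 84.2% | 10.7 |
| 36/48 | 75% | 61.2 to 85.1% | 11.9 |
| 36/60 | 60% | 47.4 to 71.4% | 12.0 |
| 29/48 | 60.4% | 46.3 to 73.0% | 13.3 |

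**Chance of meeting each rule.** Exact binomial P(X ≥ r | n, p). For 75%, r = 45 of 60 or 36 of 48. For 60%, r = 36 of 60 or 29 of 48.

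| Rule | True rate | n = 48 | n = 60 |
|---|---|---|---|
| 75% | 65% | 0.09 | 0.07 |
| 75% | 70% | 0.28 | 0.24 |
| 75% | 75% | 0.58 | 0.57 |
| 75% | 80% | 0.85 | 0.87 |
| 60% | 50% | 0.10 | 0.08 |
| 60% | 55% | 0.27 | 0.26 |
| 60% | 60% | 0.54 | 0.56 |
| 60% | 65% | 0.79 | 0.83 |

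At sizes between 48 and 60, rounding the required count up to a whole person moves these figures. For true 70% against the 75% rule, the range over n = 48 to 60 is 0.18 to 0.28.

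**Both retention rules together.** With true rates of 80% and 65%, the probability of staying from 2 to 6 months is 0.65/0.80 = 0.8125. At n = 60,

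P(both met) = Σ over x ≥ 45 of P(X = x | 60, 0.80) × P(Y ≥ 36 | x, 0.8125) = 0.775,

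so at least one rule is missed with probability 0.225. At n = 48 the miss probability is 0.26, and over n = 48 to 60 it runs from 0.225 to 0.30.

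With both true rates exactly at target (75% and 60%, conditional 0.60/0.75 = 0.80), both rules are met with probability 0.44 at n = 48 and at n = 60.

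**What sample size changes.** At n = 600, true 70% meets the 75% rule with probability 0.004, against 0.24 to 0.28 at n = 60 and 48. True 75% meets it with probability 0.52, close to the 0.57 to 0.58 seen here.

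**The case against.** A reader might infer that this pilot's verdict is a coin toss because it is small. The documents do not support that. Any single cut-off is met about half the time when the truth equals it, even with 6,000 participants (0.51). The roughly 50% figure also belongs to one criterion at a time. For both retention rules it is 0.44, and only on the 6-month reading. Nor is feasibility decided on percentages alone, since one criterion is qualitative.

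Other points carry weight:
- This is a condensed article, and intervals may be specified in a fuller document that is not shown. Their absence here is therefore weak evidence. The single-cut-off rule, however, is stated in the article itself.
- The rule is not indiscriminate. Ten points below target, the 75% rule is met only 7 to 9% of the time.
- Counts let any reader derive an interval, the Trial Steering Committee includes statistical expertise, and nothing follows automatically from the verdict.
- A tempting remedy, calling every result whose interval spans the cut-off conditionally feasible, would loosen the criteria. At n = 60 it would cover 39/60 to 51/60 for the 75% rule. At a true rate of 65%, the chance of a favourable label would rise from 7% to 56%.

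These points limit the claim and rule out that remedy. They do not remove the error rates five points either side of target, which do come from the sample size and which the stated rule ignores.

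**Conclusion.** The concern holds in a limited form. The stated rule gives a flat verdict on retention rates whose 95% intervals at the cut-off are about ±11 to 13 points wide. It passes true 2-month retention of 70% about one time in four (0.24 at n = 60, 0.28 at n = 48). On the 6-month reading, it fails a trial five points above both targets about one time in four (0.225 at n = 60, 0.26 at n = 48).

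The single-rule figures need only the binomial model. The joint figures also rest on the 6-month reading and on nested retention. Read literally, with both cut-offs at 2 months, the 60% criterion is redundant. Only the 75% rule then matters, and true 80% retention misses it 13% of the time at n = 60 and 15% at n = 48. The duplicated time point is thus an error in its own right, because it leaves the second criterion undefined.

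This is a matter of reporting and interpretation. It does not show that 60 participants is the wrong number or that the cut-offs are wrong.

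**What to change.** **Analysis plan.** Report each feasibility proportion (consent, retention, therapy uptake, outcome completion) with a 95% Wilson interval overall. For retention and outcome completion, do so by arm as well.

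**Feasibility criteria.** Keep the cut-offs on the observed percentages. Add that each retention result is stated with its interval and that the report says when the interval includes the cut-off. A narrow pass or miss then goes to the Trial Steering Committee as uncertain and not as a definitive verdict. Do not attach a conditional-feasibility label to every result whose interval spans the cut-off.

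**Time point.** Correct the repeated 2 months so that the second retention criterion has a defined time. The Design section's only later contact assessment is at 6 months.

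**Cost.** A few sentences and simple computation, with no new data. The downside is a less clear-cut verdict near the cut-offs.
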